****Methods/design**:**

This is a pragmatic, cluster-randomized controlled trial with blinded outcome assessment and embedded qualitative process evaluation. Patients from one health region in Ontario, Canada who undergo a coronary angiogram during their admission for ST-elevation myocardial infarction and who survive their initial hospitalization will be included. Allocation of eligible patients to intervention or usual care will take place within one week after the angiogram using a computer-generated random sequence. To avoid treatment contamination, patients treated by the same family physician will be allocated to the same study arm. The intervention consists of recurrent, personalized, paper-based educational messages and reminders sent via post on behalf of the interventional cardiologist to the patient, family physician, and pharmacist urging long-term adherence to secondary prevention medications. The primary outcome is the proportion of patients who report in a phone interview taking all relevant classes of cardiac medications at twelve months. Secondary outcomes to be measured at three and twelve months include proportions of patients who report: actively taking each cardiac medication class of interest (item-by-item); stopping medications due to side effects; taking one or two or three medication classes concurrently; a perfect Morisky Medication Adherence Score for cardiac medication compliance; and having a discussion with their family physician about long-term adherence to cardiac medications. Self-reported measures of adherence will be validated using administrative data for prescriptions filled.

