### **Outcomes**

The primary outcome is the proportion of living patients who describe taking all cardiac medication classes of interest measured at twelve months. This type of ‘all-or-none’ measure has been recommended for evaluating quality improvement interventions, especially related to medication utilization [43]. Specifically, we will assess whether patients are taking a statin, beta-blocker, angiotensin modifier (ACE or ARB), and aspirin at twelve months. All STEMI patients have reasonable evidence supporting these medications [3]; we anticipate that randomization will balance those patients for whom evidence is less clear or who might have contraindications to any of these medications.

We will also assess whether patients are taking these four medication classes plus a secondary antiplatelet (clopidogrel, prasugrel, or ticagrelor) at three months. Therefore, patients at three months will be dichotomized as to whether or not they are taking all five cardiac medication classes, and at twelve months they will be dichotomized according to whether they are taking all four relevant medication classes. The difference in the number of medication classes considered at three and twelve months relates to uncertainty in the evidence regarding the appropriateness of a secondary antiplatelet at this timeframe. Additional secondary outcomes include a comparison of: the proportion of patients who report actively taking each cardiac medication class of interest (item-by-item) at three and twelve months; the proportion of patients who report stopping medications due to side effects at three and twelve months; the proportion taking one or two or three medication classes concurrently at three and twelve months; and the proportion of patients with a perfect Morisky Medication Adherence Score (MMAS) for cardiac medication compliance at three and twelve months. The MMAS is a brief, standardized adherence questionnaire which excellent reliability [44], and has been shown to be predictive of cardiovascular medication adherence [45] and to be associated with control of blood pressure and cholesterol [44,46]. In addition, all patients will be asked at three months and twelve months whether they had a discussion with their family physician during past three months in which the provider had encouraged long-term cardiac medication compliance.

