### **Analysis**

Descriptive statistics will be calculated for all variables of interest: continuous variables with a normal distribution will be summarized using means and standard deviations (medians and inter-quartile ranges in the case of skewed distributions), whereas categorical variables will be summarized using frequencies and proportions.

We hypothesize that the intervention will result in a greater proportion of patients who report taking each cardiovascular medication class of interest at 12 months post-angiography. The absolute difference in proportions will be calculated for all primary and secondary dichotomous outcomes, together with 95% confidence intervals adjusting for clustering by family physician [48]. The statistical significance of differences between arms will be evaluated using chi-squared tests, adjusted for clustering by family physician.

Exploratory multivariable analyses will be carried out using generalized estimating equations (GEE) to identify potential baseline predictors of adherence. Potential effect modification by treatment—medical management versus coronary artery bypass graft (CABG) versus angioplasty—and attendance at cardiac rehabilitation will be explored by including interactions between these two variables and group. It is plausible that this analysis will suggest a need for tailored interventions for these subgroups. A further exploratory analysis will be conducted focusing on patients who reported taking all five cardiac medication classes and had perfect MMAS scores at three months using a multivariable model to examine covariates predicting late-onset discontinuation. In addition, a planned sensitivity analysis will exclude those patients who did not have a family physician, as we would expect such patients to be more likely to discontinue their cardiac medications.

Analyses will be performed on an intention-to-treat basis. No interim analyses are planned. All analyses will be carried out using the SAS Version 9.2 statistical program (SAS Institute, Cary, NC, USA).

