### **Sample size**

The sample size for this design is based on the following assumptions: an assumed absolute increase in the proportion of patients taking all four cardiovascular medication classes of 11% at twelve months post-STEMI; an estimated control group proportion of 50%, and a variance inflation factor of 1.02 (derived from an intra-cluster correlation coefficient of 0.019 calculated from data in the SMART-AMI registry and assuming an average cluster size of 1.2 based on pilot data). To achieve 80% power to detect a significant main effect of the intervention using a Chi-squared test at the 5% level of significance, 652 patients would be required. We will randomize 815 patients to account for an estimated participation rate of 80% at the 12-month follow-up. This dropout rate is conservative based on similar studies at the HIU where the participation rate has been greater than 90% over even longer time periods [40].

The expected effect size is slightly higher than the effect seen in the previous Canadian trial to account for the fact that the intervention is multifaceted (directed at both physician and patient) and occurring later post-STEMI (reducing the expected control group rate and therefore the possibility of a ceiling effect). Based on this sample size calculation, and the rate of STEMI patients presenting to the HIU, we anticipate that it will take approximately 15 months to complete the recruitment for this study.

We will use a kappa statistic to assess agreement between the self-report of the primary outcome and the corresponding objective data from the Ontario Drug Benefit database. Based on an anticipated overall proportion of 56% at 12 months (average of intervention and control arm) and an anticipated kappa of 0.88, we would consider acceptable agreement if the lower limit of the 95% confidence interval around kappa does not drop below 0.80. Therefore we will evaluate validity of the primary outcome in a random selection of 138 patients aged 65 or greater.

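### The one-to-three-classes secondary outcome has no fixed direction, and at three months it leaves patients on four of five classes in the same unlabelled remainder as patients on none (minor)

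*Protocol article*

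**What the plan says.** The Outcomes section counts a different number of classes at the two calls. At three months, "patients at three months will be dichotomized as to whether or not they are taking all five cardiac medication classes"; at twelve months, "at twelve months they will be dichotomized according to whether they are taking all four relevant medication classes". The twelve-month dichotomy is the primary outcome.

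Two other secondary outcomes describe incomplete use. One is item by item: "the proportion of patients who report actively taking each cardiac medication class of interest (item-by-item) at three and twelve months". The other is "the proportion taking one or two or three medication classes concurrently at three and twelve months", which the Abstract repeats in the same terms ("taking one or two or three medication classes concurrently"). The same one-to-three range is used at both times.

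The Analysis section then says: "The absolute difference in proportions will be calculated for all primary and secondary dichotomous outcomes". Cluster-adjusted 95% confidence intervals and chi-squared tests go with these differences. The only directional hypothesis given there concerns single classes: "We hypothesize that the intervention will result in a greater proportion of patients who report taking each cardiovascular medication class of interest at 12 months". No direction is given for the one-to-three outcome.

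**The concern.** There are two problems.

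1. **Direction.** A patient can leave the one-to-three range upwards, by reaching the full set, or downwards, by stopping everything. A difference between arms in that proportion, with its interval and p-value, therefore does not say by itself which arm persisted better.

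2. **Fit to the three-month count.** When four classes count, one to three covers every partial state. When five count, it leaves out four of five. That patient is a failure on the all-five outcome but is not in the range, and so shares an unlabelled remainder with patients taking nothing. These are nearly the best and the very worst results on the scale.

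What is at stake is the reading of one tested secondary outcome. The primary result does not depend on it.

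**Working it through.** **The plan's own figure.** The Sample size section assumes 50% in the control arm and "an assumed absolute increase in the proportion of patients taking all four cardiovascular medication classes of 11% at twelve months post-STEMI", so 50% against 61%. With a two-sided 5% level (the sidedness is assumed) and 80% power:

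n per arm = [1.960·√(2 × 0.555 × 0.445) + 0.842·√(0.50 × 0.50 + 0.61 × 0.39)]² / 0.11² = 319.2, rounded up to 320.

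The total is 640; 640 × 1.02 = 652.8 (stated 652); 652 / 0.80 = 815 (stated 815). The figure reproduces and does not depend on the outcome discussed here. It gives about 326 analysed per arm.

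**Twelve months (four classes).** Let P(j) be the proportion taking exactly j classes. Then P(1–3) = 1 − P(0) − P(4). The distributions below are assumed; only the 50% and 61% for all four come from the plan.

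| Scenario | 0 | 1 | 2 | 3 | 4 | P(1–3) | Mean classes | At least 3 |
|---|---|---|---|---|---|---|---|---|
| Control | 5% | 5% | 12% | 28% | 50% | 45% | 3.13 | 78% |
| Benefit: 11 points more on all four | 5% | 3% | 9% | 22% | 61% | 34% | 3.31 | 83% |
| Harm: 11 points more on none | 16% | 3% | 9% | 22% | 50% | 34% | 2.87 | 72% |

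Both scenarios give −11 points on the band. The standard error is √[(0.45 × 0.55 + 0.34 × 0.66)/326 × 1.02] = 0.0384, so z = 0.11/0.0384 = 2.86 and p is about 0.004 in both.

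Reading the outcome as three separate exact proportions does not help: exactly three goes from 28% to 22% in both scenarios, exactly two from 12% to 9%, and exactly one from 5% to 3%. A cumulative reading does give a direction (last column), but the article does not say *at least*.

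The primary outcome settles the matter at this time point. It is 61% under benefit and 50% under harm, and P(0) follows as 1 − P(4) − P(1–3): 5% and 16%.

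**Three months (five classes).** Assume that the band counts all five classes. Then P(1–3) = 1 − P(0) − P(4) − P(5), and the two class-count outcomes give only the sum P(0) + P(4). The distributions are again assumed.

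| Scenario | 0 | 1 | 2 | 3 | 4 | 5 | P(1–3) | P(0) + P(4) | Mean | At least 4 |
|---|---|---|---|---|---|---|---|---|---|---|
| Control | 3% | 3% | 7% | 15% | 22% | 50% | 25% | 25% | 4.00 | 72% |
| Benefit: 11 points up to four | 3% | 2% | 4% | 8% | 33% | 50% | 14% | 36% | 4.16 | 83% |
| Harm: 11 points down to none | 14% | 2% | 4% | 8% | 22% | 50% | 14% | 36% | 3.72 | 72% |

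All-five use is 50% and the band is 14% in both scenarios, so these two outcomes together cannot tell them apart.

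**What the item-by-item results add.** The five item proportions sum to the mean number of classes. A patient in the band contributes between one and three classes, so

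[mean − 5·P(5) − 3·P(1–3)]/4 ≤ P(4) ≤ [mean − 5·P(5) − P(1–3)]/4.

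- Benefit: (4.16 − 2.50 − 0.42)/4 = 31% to (4.16 − 2.50 − 0.14)/4 = 38%, capped at 36% by P(0) + P(4). The proportion on none is then 0% to 5%.
- Harm: (3.72 − 2.50 − 0.42)/4 = 20% to (3.72 − 2.50 − 0.14)/4 = 27%. The proportion on none is then 9% to 16%.

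The item results separate these two examples. They do so indirectly and to within a range, and without a planned test of the count.

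**The case against.** The strongest reply is that no one reads this outcome alone. At twelve months the primary outcome removes the ambiguity exactly. At both times the item-by-item proportions show partial stopping directly, and they carry the stated direction at twelve months. Both arguments stand, and they are why the point is minor.

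It can also be said that the phrase may be shorthand for cumulative levels, with the coding left to a fuller document. That is possible, but the article words the outcome the same way in two places and neither says so. Even the cumulative reading stops at three, so four of five at three months would still have no level of its own.

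The harm scenarios are hypothetical, and nothing in the article suggests that mailed reminders would cause complete stopping. They show only that the measure cannot rule it out.

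A reader might go further and infer any of the following. The document does not support them.

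- *That this is the only outcome measuring partial stopping.* The item-by-item outcome measures it too. This one is the only planned outcome that counts partial use within a patient.
- *That a drop from five classes to four is invisible.* It is recorded as a failure on the all-five outcome and lowers one item proportion. It just cannot be told from a larger drop by the class-count outcomes.
- *That patients on none are not counted.* They are on the failing side of both dichotomies and are non-takers in every item. They only lack a category of their own.

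**Conclusion.** The point holds in limited form. As a band or as exact counts, the one-to-three outcome moves the same way under benefit and under harm: −11 points and p about 0.004 in either case in the twelve-month illustration. The primary outcome resolves this at twelve months. At three months the definition does not fit the five-class count, and the class-count outcomes cannot separate four of five from none; the item-by-item results narrow the gap without closing it.

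The sizes rest on assumed distributions. The structural result does not: it follows from the definitions, given that the band counts five classes at three months. If only the four core classes were meant there, a patient on all four without the second antiplatelet would still be in neither group.

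Severity is minor. It would be wrong to infer that the trial's main conclusion or its sample size of 652 analysed and 815 randomized is in doubt.

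**What to change.** Replace the one-to-three outcome with one of these, stating that higher is better:

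- an ordered comparison between arms of the number of classes taken, 0–5 at three months and 0–4 at twelve; or
- cumulative proportions taking at least one, at least two and at least three classes at both times, plus at least four at three months.

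In either case, report the full distribution of the count by arm at each call. The cumulative form keeps the planned absolute differences and cluster-adjusted tests unchanged. The ordered form needs a cluster-adjusted ordinal method to be named.

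No new data are needed, because the Data collection section already has patients list all their current medications at both calls. The cost is a small wording change to one secondary outcome, best made before the analysis.

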### **Intervention**

The intervention was developed in concert with clinical experts from both primary care and cardiology, as well as experts in knowledge translation and medical decision-making. Personalized letters sent via post to the patient and their family physician at one, five, eight, and eleven months after their angiogram, signed by the interventional cardiologist (see Additional file 1: Appendix A for prototype). The letter for the family physician names the patient and provides brief evidence in support of long-term medication use for these patients. This was reviewed and edited with a series of family physicians from a different area of the province.

The patient letter provides a review of the importance and role of each of the cardiac medications and urges short- and long-term adherence (see Additional file 1: Appendix B for prototype). This educational aspect is designed to address knowledge and beliefs about medication use as a potential cause of poor adherence. The intervention explicitly encourages discussion of medication adherence with the family physician by asking patients to bring the letter to their family physician. It also asks patients to deliver the final page of their letter to their pharmacist; this page is written to the pharmacist urging them to participate in promoting long-term adherence. The intention is to facilitate recurrent discussions with primary care providers that emphasize long-term adherence and to address coordination of care and continuity of information as barriers to medication persistence. This letter was developed with iterative evaluations of understanding and acceptability amongst a series of cardiology patients at the HIU. The language in the patient letter is simplified to a grade six-level.

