The timing of the intervention was specifically chosen based on the preliminary data obtained from the SMART-AMI trial demonstrating suboptimal rates at 90 days. Furthermore, literature (referenced above) demonstrates that adherence starts decreasing by thirty days and continues to decrease in an almost linear fashion. Finally, the common practice in Ontario is for pharmacists to dispense medications for no more than three months at a time (regardless of duration of the prescription ordered by the physician). Therefore, we decided to deliver the intervention at regular intervals (1, 5, 8, and 11 months post-STEMI) corresponding to the likely time periods prior to patients requiring a prescription renewal/refill. In pilot testing the intervention with family physicians and patients, we determined that sending the full letter too frequently would be undesirable and that the physicians in particular did not want to have monthly reminders. At the same time, close examination of data from Ontario indicated large stepwise declines in adherence at 30 and 60 days post-STEMI. To address this, patients will be provided an additional postcard type reminder two months post-STEMI (see Additional file 1: Appendix C).

In summary, the unique aspects of the intervention compared to usual care include the following: the letter to the primary care provider is personalized and includes a summary of the evidence in support of long-term adherence and represents a recurrent form of contact between the cardiologist and the primary care provider; the letter to the patient use clear language suitable for a broad range of health literacy levels and was iteratively refined with input from patients in the target population, features content that attempts to address adherence-related beliefs, and provides explicit, actionable instructions to discuss the matter with the family physician as well as a summary to be given to the outpatient pharmacist to facilitate coordination of renewals.

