### **Allocation**

The randomization schedule was computer-generated by a statistician independent of the study, using a permuted block design with randomly varying block lengths of four, six, or eight. Eligible patients are randomly allocated to one of the two treatment arms. Although enrolment of more than one patient treated by a particular family physician is expected to occur infrequently, randomization will be carried out to ensure that, once a patient from any family physician is randomized, all future patients seen by that family physician will automatically be assigned to the same arm. This is necessary to avoid contamination (with one family physician having patients in different intervention arms). Roughly one-half of patients will be allocated to each study arm (the actual allocation ratio will depend on the size of the clusters). Based on pilot data, we anticipate that approximately 10% to 15% of patients will not have a family physician. In keeping with the pragmatic design of the trial, a patient without a family physician will be included (receiving only the patient-level intervention).

Randomization is delayed by one week (after the angiogram) to permit time to identify and exclude patients with in-hospital death. Randomization will continue until the target sample size is achieved. The anticipated duration of enrolment is 15 months. The allocation sequence will be concealed from the investigators and outcome assessors; only the study coordinator who will be sending out the letters will have access to the un-blinded allocation list.

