### **Data collection**

Baseline patient characteristics will be obtained from standard patient-registry information at the HIU. This includes demographic information, comorbidities, and the findings at the time of angiography.

Outcomes will be assessed 3 and 12 months post-index angiogram through patient phone calls by a research coordinator associated with the HIU who will be trained expressly for this function. The research coordinator conducting the phone calls will not have access to the allocation list. The calls are made on behalf of the treating cardiologist at the HIU, and all patients will be encouraged to review cardio-protective meds with their family physician. The phone call follow-ups will ask patients to list their current, daily medications (and doses) without specific prompting in order to reduce bias. Attempts will be made to contact patients for a maximum of 30 days prior to being considered lost-to-follow-up. Reasons for loss-to-follow-up will be tracked.

For a sample of patients aged 65 and older, the Ontario Drug Benefit database will be used to examine the accuracy of the self-reported primary outcome and to further evaluate adherence using the medication possession ratio over the preceding year, which has been shown to be associated with both pill counts and clinical effects [47].

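### The look-back of the 3-month discussion question reaches into the month before the first letter, which can dilute the between-arm difference in this one secondary outcome

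*Protocol article*

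**What the plan says.** Under Outcomes, "all patients will be asked at three months and twelve months whether they had a discussion with their family physician during past three months", and a discussion counts only if it was one "in which the provider had encouraged long-term cardiac medication compliance". Data collection sets the clock: "Outcomes will be assessed 3 and 12 months post-index angiogram through patient phone calls". It also allows late contact: "Attempts will be made to contact patients for a maximum of 30 days prior to being considered lost-to-follow-up".

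Under Intervention, letters go out "at one, five, eight, and eleven months after their angiogram, signed by the interventional cardiologist". Between the first letter and the 3-month call there is one further contact: "patients will be provided an additional postcard type reminder two months post-STEMI". Under Allocation, randomization takes place one week after the angiogram.

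The Objectives section makes the prompting of such discussions a secondary objective. The Intervention section says that the patient is asked to take the letter to the family physician, and that the intention is for discussions to recur, not to happen only once.

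**The concern.** The look-back of three months and the call at three months are both fixed, and together they place the start of the window at the angiogram. The letter that is meant to prompt the discussion arrives a month later. The item is a simple yes or no, so a patient whose physician encouraged long-term use in the first month is already a yes, whatever the letter does afterwards. Nothing has been sent by then, so such patients should be equally common in both arms.

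This item is the direct measure of the secondary objective. The 3-month call is also the only early test of whether the letter starts a conversation. A small or null difference there could partly reflect the window and not the letter, and the trial intends to use null findings to improve the intervention.

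**Working it through.** **Timing.** All times are in months from the index angiogram.

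| Event | Time | Section |
|---|---|---|
| Randomization | one week | Allocation |
| First letter | 1 | Intervention |
| Postcard to patient | 2 | Intervention |
| 3-month call, on time | 3, window 0 to 3 | Data collection, Outcomes |
| 12-month call, on time | 12, window 9 to 12 | Data collection, Outcomes |

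Take a month as 30 days and the contact attempts as running for up to 30 days after the 3-month date. For a call L days late, the share of the window before the first letter is max(0, 30 - L)/90:

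- L = 0: 30/90 = 33%
- L = 15: 15/90 = 17%
- L = 30: 0/90 = 0%

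At 12 months the window lies wholly after letters began. The month-8 letter precedes it and the month-11 letter falls inside it, so the problem is confined to the 3-month item.

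**The plan's own figure.** The article gives no power calculation for the discussion outcome. Its primary calculation reproduces: 50% vs 61%, two-sided 5%, 80% power gives 320 per arm, and 640 × 1.02 = 652.8 against the stated 652; 652/0.80 = 815. From this I take 652/2 = 326 respondents per arm as an illustrative size. It rests on 80% participation at 12 months; the article gives no separate 3-month figure.

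**Dilution.** Let q be the share with an encouraging discussion before the first letter, equal in both arms. Let r0 and r1 be the shares with one afterwards, control and intervention. If early and later discussions are independent, the measured proportion in each arm is 1 - (1 - q)(1 - r), so the measured difference is (1 - q)(r1 - r0).

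The article gives none of q, r0 or r1. Assume r0 = 30% and r1 = 45%, and let q range from 0% to 70%. Power is by the normal approximation, 326 per arm, two-sided 5%:

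| q | Control | Intervention | Difference (points) | Power |
|---|---|---|---|---|
| 0% | 30.0% | 45.0% | 15.0 | 98% |
| 10% | 37.0% | 50.5% | 13.5 | 94% |
| 20% | 44.0% | 56.0% | 12.0 | 87% |
| 30% | 51.0% | 61.5% | 10.5 | 77% |
| 50% | 65.0% | 72.5% | 7.5 | 54% |
| 70% | 79.0% | 83.5% | 4.5 | 31% |

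Applying the variance inflation of 1.02 lowers each power by less than one percentage point.

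**Without independence.** Suppose instead that letters prompt only patients with no earlier discussion. The post-letter difference is then itself (1 - q) × 15 points, and the two windows show the same difference:

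- q = 30%: 10.5 points in both. Power is 80% with a post-letter window (30.0% vs 40.5%) and 77% with the three-month window (51.0% vs 61.5%).
- q = 50%: 7.5 points in both. Power is 53% (30.0% vs 37.5%) and 54% (65.0% vs 72.5%).

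In that case a shorter window gains essentially nothing.

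**The case against.** The strongest defence is that the three-month window is a legitimate quantity: did the patient have an encouraging discussion in the first three months? It is applied identically in both arms and creates no false difference. If some control patients have already had the talk, a smaller contrast is the true added value over usual care. This stands in part. It is weakened because the window opens a week before randomization, and because the letters aim at repeated discussions, which a single early yes can hide.

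Several stronger readings are tempting and are not supported:

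- *Any routine early visit counts as a success.* It does not; the physician must have encouraged long-term compliance.
- *The loss of power is large.* The low figures need half or more of all patients to have had an encouraging discussion within a month. The article gives reasons to expect fewer: 10% to 15% are anticipated to have no family physician, discharge summaries often omit medication information, and communication between hospital and primary care is described as poor. Part of that month may also be spent in hospital.
- *The factor (1 - q) always applies.* It depends on independence, as shown above.
- *The two time points must measure the same thing.* The planned analyses compare arms at each time point, so a difference in meaning between 3 and 12 months harms no stated comparison.

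**Conclusion.** The mismatch in dates is real and follows from the article alone: up to one third of the 3-month look-back precedes the first letter, falling to none for a call 30 days late. Any effect is dilution towards no difference, in one secondary outcome at one time point. The primary outcome, the sample size and the 12-month item are untouched.

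The size cannot be determined from the document. Under independence the difference retains a fraction (1 - q); with the assumed rates, the loss of power is modest at q of 10% to 20% and becomes serious only at about 50% and above. If letters reach only patients without an earlier discussion, there is essentially no loss. A reader might infer that a null 3-month result would be uninterpretable; that goes further than the document allows. This is a worthwhile, inexpensive improvement and not a flaw that threatens the trial's conclusions.

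**What to change.** At the 3-month call, in both arms, ask about discussions since one month after the angiogram, with the coordinator stating that calendar date. For an on-time call this is about the past two months. Use the answer as the 3-month discussion outcome, and leave the 12-month question unchanged.

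The cost is one changed line in the 3-month call script. There are two small downsides. The look-back length then differs between the two calls, which matters little because each is compared only between arms. Control patients also have no event at one month to anchor their recall, which is why the coordinator should state the date.
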